### **Cost-Effectiveness Measures**

To establish the cost-effectiveness of the mentoring package, the following will be assessed:

- Referral on for secondary care opinion or intervention, or for diagnostic imaging.
- Use of prescription medication.
- Costs of physiotherapy intervention (number and type of attendances)
- Return to work
- Costs associated with the training of physiotherapists

The rationale and description of this element of the study is developed and explored in the economic evaluation section along with details of analysis.

The quantitative data collection for this study is summarized below in table 1.

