| 
Work Status:
 
Employed 
 
Self-employed 
 
Unemployed 
 
Carer 
 
Retired 
 
Student 
 
Please could you indicate (✓) which income band your approximate annual household income would fall within:
 

Less than £10,000		£4,000 - £49,000		

£10,00 - £19,000		£50,000 - £59,000		

£2,000 - £29,000		£60,000 - £69,000		

£30,000 - £39,000		£70,000 or above		

 | Less than £10,000                                                                                                                                                                                                                                                                                                                                                                                                                                                                                                                                                                                                                                                                                                                                                                                                                                                                   |                   | £4,000 - £49,000 |  | £10,00 - £19,000 |  | £50,000 - £59,000 |  | £2,000 - £29,000 |  | £60,000 - £69,000 |  | £30,000 - £39,000 |  | £70,000 or above |  | 
Please choose a statement below that best describes your main work situation over the last 6 months. Tick only one box.
 
 I have been working my usual hours and duties
 
 I am working my usual hours, but I have been unable to do some/all of my usual duties because of my pain / musculoskeletal condition.
 
What proportion of your duties have you stopped doing? Please state a percentage:.....%
 
 I am doing all my usual duties, but I have been unable to work my usual hours because of my pain / musculoskeletal condition.
 
How many hours less have you worked per week? ..... hours
 
 I am currently unable to work because of this problem.
 
 I am currently unable to work because of another problem.
 
Sick Pay / Benefits:
 
Are you currently receiving any of the following because of this problem:
 
Employer's sick pay                      Yes  No 
 
Statutory sick pay                        Yes  No 
 
Disability living allowance              Yes  No 
 |

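### The baseline work-situation item mixes a six-month stem with present-tense options under a one-tick rule and omits two states, so return to work is open to misclassification

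*Protocol*

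**What the plan says.** The protocol's Cost-Effectiveness Measures section lists "Return to work" among the items to be assessed and does not define it. The form that records ability to work is the baseline Patient Outcome Questionnaire in Appendix A, Section A (Personal and Work Information). Its stem reads "Please choose a statement below that best describes your main work situation over the last 6 months", followed by "Tick only one box". The five options are:

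1. "I have been working my usual hours and duties"
2. "I am working my usual hours, but I have been unable to do some/all of my usual duties" (with a percentage of duties stopped)
3. "I am doing all my usual duties, but I have been unable to work my usual hours" (with hours lost per week)
4. "I am currently unable to work because of" this problem
5. The same words, but for another problem

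Two other questions in the same section bear on the point. Work Status offers employed, self-employed, unemployed, carer, retired and student. A sick-pay and benefits question begins "Are you currently receiving any of the following because of this problem" and lists employer's sick pay, statutory sick pay and disability living allowance.

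Table 6 in Economic Evaluation Methods refers to baseline, discharge and 12-month questionnaires. The work items of the last two cannot be seen in the text at hand.

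**The concern.** A return-to-work measure needs two facts: who was off work because of the problem at the start, and who among them was back at work later. The baseline form supplies the first. If its wording lets a patient who is off work today be filed as working, that patient leaves the group at risk of returning, and no later form puts the patient back.

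A statistical analysis plan can define the measure. It cannot recover a status that the form did not capture clearly, so the fault belongs to the form and is best dealt with before patients complete it.

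What is at stake is modest: one economic measure, plus the description of partial work loss.

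**Working it through.** The plan gives no figure for this measure, so there is none to reproduce. The check sets the options against the states a patient can be in and against the time frame of the stem.

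**Time frame.** The stem looks back six months. Option 1 is worded to match. Options 2 and 3 open in the present tense, and options 4 and 5 refer to the present. Four of the five options therefore do not clearly share the stem's frame.

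| Patient in paid work | Box by the stem | Box by the option's own wording |
|---|---|---|
| Working normally throughout | 1 | 1 |
| Off work throughout because of this problem | 4 | 4 |
| Worked normally, off for the last three weeks because of this problem | 1 | 4 |
| Off most of the six months, now back as usual | none that is true as worded | 1 at best |

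The first two rows are unambiguous. In the third, both boxes are defensible and only one may be ticked. If option 1 is ticked, a patient who is off work enters as working. In the fourth, no box describes a past absence that has ended: a working box loses the absence, and option 4 is untrue on the day.

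**Hours and duties.** A working patient can have full or reduced hours and full or reduced duties, which gives 2 × 2 = 4 states. Full/full is option 1, full/reduced is option 2 and reduced/full is option 3. Reduced/reduced has no box. Either neighbouring box still records the patient as at work, so the off-work/at-work split is not disturbed. What is blurred is the degree of partial loss, because only one of the two follow-on figures belongs to the box ticked.

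**Not in paid work.** Four of the six Work Status categories (unemployed, carer, retired, student) have no matching box, and no skip instruction joins the two questions. These patients can still be identified from Work Status and removed from the denominator.

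**What the time-frame fault could do (assumed figures, for direction only).** Suppose 20 workers are off work at baseline because of the problem and 10 return, a true rate of 10/20 = 50%. Suppose 5 recent-onset patients tick option 1 and so drop out of the denominator, leaving 20 − 5 = 15.

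- If all 5 would have returned: (10 − 5)/15 = 33%.
- If none would have returned: 10/15 = 67%.
- If they return at the same 50% on average: (10 − 2.5)/15 = 50%, with no bias but fewer patients.

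The error therefore depends on how many patients are misfiled and on whether they return at a different rate from the rest. The documents give neither figure. Any misfiled patient recovered through the sick-pay question narrows the range.

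**The case against.** The strongest reply is that the form already holds most of what is needed, and much of it stands.

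- **Non-workers.** A reader might infer that retired, unemployed, student and carer patients would swell the off-work group and depress the recorded rate. The documents do not support that. Work Status is on the same page, and the form separates this problem from another problem. Excluding non-workers removes that distortion. The exclusion is slightly imperfect, because the unemployed category gives no reason and may include someone who lost work through this problem.
- **Sick pay.** A patient who went off work three weeks ago and ticked option 1 may be identified by the question on current payments. This is a real cross-check but a partial one: it records receipt of payments, not work status, and misses anyone who is off work without them.
- **Follow-up forms.** A reader might infer that return itself is recorded wrongly at discharge and 12 months. Those forms are not visible, so this cannot be said. What can be said is that, if the six-month stem is reused at discharge, the look-back could reach into the period before treatment.
- **Comparison between training conditions.** A reader might infer that the comparison of mentored with usual training is biased. That would require misfiling to differ between control and intervention periods. The Blinding section states that patients will not know whether their physiotherapist has been trained, and nothing in the documents shows such a difference.
- **Importance.** Return to work appears in no hypothesis, is neither the primary outcome nor one of the listed secondary outcomes, and is absent from the cost modules in Table 6. The economic analysis takes a UK NHS perspective. Leaving its operational definition to an analysis plan is normal and is not criticised here.

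None of this resolves the conflict between stem and options for workers who recently went off work.

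**Conclusion.** The item is not exhaustive and mixes two time frames under a one-tick rule. Baseline off-work status, and with it the return-to-work measure, is open to misclassification that the sick-pay question corrects only in part. The time-frame conflict is the part that matters. The missing box for both reductions affects only the grading of partial work loss, and the missing box for non-workers can be handled through Work Status.

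The stronger conclusion that return to work cannot be measured is not supported: patients off work throughout the six months have a clear box, non-workers can be excluded, and a partial cross-check exists.

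The size cannot be derived from the documents. The conclusion assumes that the form is used as printed and that some patients attend soon after going off work or returning. It is a minor point about one cost-effectiveness measure. The PSFS outcome and its power calculation are untouched.

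**What to change.** Before baseline forms are completed:

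1. Ask for work status on the day of completion, with every option in the same tense, and use identical wording at the first appointment, discharge and 12 months.
2. Add a box for patients not in paid work and a box for both hours and duties reduced, the latter with both follow-on figures.
3. Calculate return to work among patients in paid work who were off work because of this problem at the first appointment. Keep the sick-pay question as a cross-check.

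The cost is one reworded item with two more boxes, the same check on the two follow-up forms, and one line of definition. The small loss is the six-month summary of work situation. If the economic analysis needs it, ask it as a separate question.

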
**Section B: Healthcare Information:**

This section tells us which health services and medication you have used for your pain/musculoskeletal condition

1. During the last 6 months, have you been to see/made contact with any other health professional or organisation for your pain / musculoskeletal condition? (Please include both NHS and private opinions.)

**Yes** ☐ (please complete the tables below)

**No** ☐ (continue with question 2)

| NHS Consultations |                                                             |                                                                           |                                                                     |
|--------------------------|-------------------------------------------------------------|---------------------------------------------------------------------------|---------------------------------------------------------------------|
| Health care professional | Number of visits made to this person over the past 6 months | Number of telephone consultations with this person over the past 6 months | Number of visits by this person to your home over the past 6 months |
| A & E                    |                                                             |                                                                           |                                                                     |
| Counsellor               |                                                             |                                                                           |                                                                     |
| Doctor (GP)              |                                                             |                                                                           |                                                                     |
| Hospital Consultant      |                                                             |                                                                           |                                                                     |
| NHS Direct               |                                                             |                                                                           |                                                                     |
| Physiotherapist          |                                                             |                                                                           |                                                                     |
| Practice nurse           |                                                             |                                                                           |                                                                     |
| Other (please specify)   |                                                             |                                                                           |                                                                     |

| Private Consultations |                                                             |                 |
|------------------------------|-------------------------------------------------------------|-----------------|
| Health care professional     | Number of visits made to this person over the past 6 months | Costs of visits |
| Acupuncturist                |                                                             |                 |
| Chiropractor                 |                                                             |                 |
| Hospital Consultant          |                                                             |                 |
| Osteopath                    |                                                             |                 |
| Physiotherapist              |                                                             |                 |
| Other (please specify)       |                                                             |                 |

2. During the last 6 months, have you received any diagnostic tests, investigations (e.g. blood test, X rays, MRI scan) because of your pain/ musculoskeletal condition?

**Yes** ☐ (please complete the table below)

**No** ☐ (continue with question 3)

| Date (if known) | Type of treatment/investigation |
|-----------------|---------------------------------|
|                 |                                 |
|                 |                                 |
|                 |                                 |
|                 |                                 |

3. During the last 6 months have you been admitted to hospital (as an in-patient or out-patient) because of your pain/ musculoskeletal condition?

**Yes** ☐ (please complete the table below)

**No** ☐ (continue with question 4)

| Date
(if known) | Inpatient
Location | Number of days
in hospital | Outpatient
attendance |
|--------------------|-----------------------|-------------------------------|--------------------------|
|                    |                       |                               |                          |
|                    |                       |                               |                          |
|                    |                       |                               |                          |
|                    |                       |                               |                          |

4. During the last 6 months have you been prescribed any medication for your pain/ musculoskeletal condition?

**Yes** ☐ (please complete the table below)

**No** ☐ (continue with question 5)

| Name of medicine      | Number of tablets to
be taken per day | Strength of
each tablet | Number of
days supplied |
|-----------------------|------------------------------------------|----------------------------|----------------------------|
| e.g. Ibuprofen | e.g. 6                            | e.g. 200mg          | e.g. 7              |
|                       |                                          |                            |                            |
|                       |                                          |                            |                            |
|                       |                                          |                            |                            |
|                       |                                          |                            |                            |
|                       |                                          |                            |                            |
|                       |                                          |                            |                            |

5. During the last 6 months, have you bought any over-the-counter medicines, other treatments, or equipment to help treat your pain/ musculoskeletal condition?

**Yes** ☐ (please complete the table below)

**No** ☐ (please continue with Section D)

(Please include painkillers, anti-inflammatory drugs/gels/creams/sprays etc; herbal or complementary remedies including massage; and equipment e.g. TENS machine)

| Item or other remedy bought | Total cost (£) |
|-----------------------------|----------------|
|                             |                |
|                             |                |
|                             |                |
|                             |                |
|                             |                |
|                             |                |

**Functional Scale:** Your physiotherapist will complete this with you to identify up to three important activities that you are unable to do or are having difficulty with as a result of your problem. Your physiotherapist will ask you some questions to help you rate how difficult those activities are.

| Activity | Initial Score: | Current Score: |
|----------|----------------|----------------|
| 1.       |                |                |
| 2.       |                |                |
| 3.       |                |                |

Please read and answer questions carefully. Do not take too long to answer the questions; however it is important that you answer every question. There is **always** a response for your particular situation.

☐ Neck
 ☐ Shoulder
 ☐ Arm
 ☐ Upper Back  
☐ Lower Back
 ☐ Leg
 ☐ Other (state)

☐ 0 days (1)      ☐ 1-2 days (2)      ☐ 3-7 days (3)      ☐ 8-14 days (4)

☐ 15-30 days (5)      ☐ 1 month (6)      ☐ 2 months (7)      ☐ 3-6 months (8)

☐ 6-12 months (9)      ☐ over 1 year (10)

☐ 0-1 weeks (1)      ☐ 1-2 weeks (2)      ☐ 3-4 weeks (3)      ☐ 4-5 weeks (4)

☐ 6-8 weeks (5)      ☐ 9-11 weeks (6)      ☐ 3-6 months (7)      ☐ 6-9 months (8)

☐ 9-12 months (9)      ☐ over 1 year (10)

0 1 2 3 4 5 6 7 8 9 10  
Not at all Extremely

| 0       | 1 | 2 | 3 | 4 | 5 | 6 | 7 | 8 | 9 | 10                         |
|---------|---|---|---|---|---|---|---|---|---|----------------------------|
| No pain |   |   |   |   |   |   |   |   |   | Pain as bad as it could be |

| 0                          | 1 | 2 | 3 | 4 | 5 | 6 | 7 | 8 | 9 | 10 |
|----------------------------|---|---|---|---|---|---|---|---|---|----|
| No pain                    |   |   |   |   |   |   |   |   |   |    |
| Pain as bad as it could be |   |   |   |   |   |   |   |   |   |    |

0 1 2 3 4 5 6 7 8 9 10  
Never Always

0 1 2 3 4 5 6 7 8 9 10

Can't decrease it at all Can decrease it completely

0 1 2 3 4 5 6 7 8 9 10

Absolutely calm and relaxed As tense and anxious as I've ever felt

0 1 2 3 4 5 6 7 8 9 10

Not at all Extremely

0 1 2 3 4 5 6 7 8 9 10  
No risk Very large risk

0 1 2 3 4 5 6 7 8 9 10

No chance Very large chance

0 1 2 3 4 5 6 7 8 9 10

Not satisfied at all Completely satisfied

---

Here are some of the things that other people have told us about their pain. For each statement, circle one number from 0 to 10 to say how much physical activities, such as bending, lifting, walking or driving, would affect your pain.

---

**14. Physical activity makes my pain worse.**

---

0 1 2 3 4 5 6 7 8 9 10  
Completely disagree Completely agree

---

**15. An increase in pain is an indication that I should stop what I'm doing until the pain decreases.**

---

0 1 2 3 4 5 6 7 8 9 10  
Completely disagree Completely agree

---

**16. I should not do my normal work with my present pain.**

---

0 1 2 3 4 5 6 7 8 9 10  
Completely disagree Completely agree

---

**Here is a list of five activities. Circle the one number that best describes your current ability to participate in each of these activities.**

---

**17. I can do light work for an hour.**

---

0 1 2 3 4 5 6 7 8 9 10  
Can't do it because of Can do it without  
pain problem pain being a problem

---

**18. I can walk for an hour.**

---

0 1 2 3 4 5 6 7 8 9 10  
Can't do it because of Can do it without  
pain problem pain being a problem

---

**19. I can do ordinary household chores.**

---

0 1 2 3 4 5 6 7 8 9 10  
Can't do it because of Can do it without  
pain problem pain being a problem

---

**20. I can do the weekly shopping.**

---

0 1 2 3 4 5 6 7 8 9 10  
Can't do it because of Can do it without  
pain problem pain being a problem

---

**21. I can sleep at night.**

---

0 1 2 3 4 5 6 7 8 9 10  
Can't do it because of Can do it without  
of pain problem pain being a problem

---

## **Me and My Health**

**INSTRUCTIONS:** For each statement below please mark an X in the box to the right that best describes how much you disagree—agree with the statement as it applies to you personally.

There are no right or wrong answers. Your answers should be what are true to you and not just what you think the physiotherapist wants you to say.

|                                                                                                                                            | Strongly Disagree        | Disagree                 | Agree                    | Strongly Agree           |
|--------------------------------------------------------------------------------------------------------------------------------------------|--------------------------|--------------------------|--------------------------|--------------------------|
| 1 When all is said and done, I am the person who is responsible for managing my health condition.                                          |  |  |  |  |
| 2 Taking an active role in my own health care is the most important factor in determining my health and ability to function.               |  |  |  |  |
| 3 I am confident that I can take actions that will help prevent or minimize some symptoms or problems associated with my health condition. |  |  |  |  |
| 4 I know what each of my prescribed medications do.                                                                                        |  |  |  |  |
| 5 I am confident that I can tell when I need to go get medical care and when I can handle a health problem myself.                         |  |  |  |  |
| 6 I am confident that I can tell doctor concerns I have even when he or she does not ask.                                                  |  |  |  |  |
| 7 I am confident that I can follow through on medical treatments I need to do at home.                                                     |  |  |  |  |
| 8 I understand the nature and causes of my health condition(s).                                                                            |  |  |  |  |
| 9 I know the different medical treatment options available for my health condition.                                                        |  |  |  |  |
| 10 I have been able to maintain the lifestyle changes for my health condition that I have made.                                            |  |  |  |  |
| 11 I know how to prevent further problems with my health condition.                                                                        |  |  |  |  |
| 12 I know how to prevent further problems when new situations or problems arise with my health condition.                                  |  |  |  |  |
| 13 I am confident that I can maintain lifestyle changes, like diet and exercise, even during times of stress.                              |  |  |  |  |

